### 2.2 Primary Objective

To investigate whether intraperitoneal local anesthetic (Ropivacaine 0.2%) administered during and up to 72 h postoperatively following cytoreductive surgery in patients with advanced stage epithelial ovarian cancer leads to an earlier start of adjuvant chemotherapy as compared to patients receiving placebo (saline).

## 2.3 Secondary Objectives

Post-operative complications, post-operative morbidity, quality of recovery, cardiac and renal impairment and overall survival.

## 2.4 Primary outcome measure

Time from surgery to start of adjuvant chemotherapy

### 2.4.1 Definition of primary outcome measure

Number of days from surgery until first infusion of adjuvant chemotherapy. First day after surgery will count as day one.

## 2.5 Secondary outcome measures

- Post-operative complications
- Post-operative morbidity
- Quality of recovery
- Cardiac and renal impairment
- Overall survival (OS) at 3- and 5-years

### 2.5.1 Definition of secondary outcome measures

Post-operative complications: Assessed with Clavien-Dindo classification up to 30 days postoperatively (44).

Post-operative morbidity: Will be assessed by the postoperative morbidity score (POMS) on postoperative day 3 and 5 (45).

Quality of recovery (QoR): Will be assessed the day before surgery and 3 days after surgery with the QoR-15 questionnaire (46, 47).

Overall survival: Survival time is calculated from the date of randomization to the date of death (all-cause), or for patients still alive to the date of last clinical follow-up or contact.

## 3 Study design

Prospective, randomized, double-blind, placebo-controlled trial.

### 3.1 Study flowchart

[figure not shown]

**Abbreviations:** FIGO, International Federation of Obstetrics and Gynecology; QoR-15, Quality of Recovery questionnaire; POMS, Postoperative Morbidity Score; C-D, Clavien Dindo

### 3.2 Schedule of events table

| Procedures                                                                                     | Enrolment/
Baseline | Day of Surgery | Post-operative day 1 | Post-operative day 3 | Post-operative day 5 | Post-operative day 30 | Day of first
chemotherapy
infusion | Day of last
chemotherapy
infusion | 6 months post-
operatively | 1 year after surgery | 3 years after surgery | 5 years after surgery |
|------------------------------------------------------------------------------------------------|------------------------|----------------|----------------------|----------------------|----------------------|-----------------------|------------------------------------------|-----------------------------------------|-------------------------------|----------------------|-----------------------|-----------------------|
| Informed consent oral and written                                                              | X                      |                |                      |                      |                      |                       |                                          |                                         |                               |                      |                       |                       |
| Inclusion and exclusion criteria                                                               | X                      |                |                      |                      |                      |                       |                                          |                                         |                               |                      |                       |                       |
| Demographics                                                                                   | X                      |                |                      |                      |                      |                       |                                          |                                         |                               |                      |                       |                       |
| Blood-samples                                                                      | X                      |                | X                    | X                    | X                    |                       |                                          |                                         |                               |                      |                       |                       |
| Quality of recovery Swe-15 Questionnaire                                           | X                      |                |                      | X                    |                      |                       |                                          |                                         |                               |                      |                       |                       |
| Randomisation                                                                                  |                        | X              |                      |                      |                      |                       |                                          |                                         |                               |                      |                       |                       |
| Record operative report                                                                        |                        | X              |                      |                      |                      |                       |                                          |                                         |                               |                      |                       |                       |
| Treatment according to randomisation                                                           |                        | X              | X                    | X                    |                      |                       |                                          |                                         |                               |                      |                       |                       |
| Removal of intraperitoneal catheter                                                            |                        |                |                      | X                    |                      |                       |                                          |                                         |                               |                      |                       |                       |
| Postoperative morbidity score (POMS)                                               |                        |                |                      | X                    | X                    |                       |                                          |                                         |                               |                      |                       |                       |
| Pain management and evaluation                                                                 |                        |                |                      | X                    |                      |                       |                                          |                                         |                               |                      |                       |                       |
| Record 30-day post-operative complications according to Clavien Dindo and definitive histology |                        |                |                      |                      |                      | X                     |                                          |                                         |                               |                      |                       |                       |
| Record primary outcome (days from surgery to start of adjuvant chemotherapy)                   |                        |                |                      |                      |                      |                       |                                          |                                         | X                             |                      |                       |                       |
| Record adjuvant treatment                                                                      |                        |                |                      |                      |                      |                       |                                          |                                         | X                             |                      |                       |                       |
| Record survival                                                                                |                        |                |                      |                      |                      |                       |                                          |                                         |                               |                      | X                     | X                     |
| AE/SAE                                                                                         |                        | X              | X                    | X                    | X                    | X                     |                                          |                                         |                               |                      |                       |                       |
| Translational part tissue (site Karolinska only)                                               |                        | X  |                      |                      |                      |                       |                                          |                                         |                               |                      |                       |                       |
| Translational part blood (site Karolinska only)                                    |                        | X  |                      |                      |                      |                       | X                            | X                           |                               | X                    |                       |                       |

Abbreviations: AE, adverse events; SAE, serious adverse events.

 Hb (g/L) CRP (mg/L), Troponin T (ng/L), Albumin (g/L), Natrium (mmol/L), Kalium (mmol/L), eGFR1 (ml/min/1,73m^2), Creatinine (micromol/L), S-Transtyretin, P-Fibrinogen, S-Prokalcitonin, CA-125 (kE/L), CEA (microg/L, only preop). see Appendix 17.4. see Appendix 17.2. Collected at beginning and end of surgery. 40 mL of blood. Before infusion of chemotherapy.

*The IPLA –OVCA trial protocol version 3.2.1, 2021-01-28*

## 4 Study enrollment

### 4.1 Screening procedure and participant identification

All women with epithelial ovarian cancer, FIGO stage III-IV can undergo screening for this trial and will be documented in a screening log. After obtaining oral and written informed consent, patients will be registered and randomized. Registration data must be entered to an electronic Case Report Form (eCRF).

### 4.2 Inclusion criteria

- Women > 18 years
- ASA I-III
- Scheduled for upfront cytoreductive surgery for stage III or IV epithelial ovarian cancer
- Signed written informed consent

### 4.3 Exclusion criteria

- Contraindication to epidural anesthesia
- Allergy to any component drugs used during epidural or intraperitoneal anesthesia (Ropivacaine, Sufentanil)
- Uncontrolled renal, liver, heart failure or ischemic heart disease
- Speech, language or cognitive difficulties
- Women in whom cytoreductive surgery is not attempted at time of upfront laparotomy due to extent of disease

### 4.4 Randomization and registration

After verification of eligibility and signed informed written consent, women will be randomised at the morning of surgery to receive either Ropivacaine or saline by equal allocation, 1:1. The randomisation procedure will be pre-stratified for participating centre (permuted block design).

The Clinical Trials Unit at Centre for Clinical Cancer Studies Theme Cancer, Karolinska University Hospital, Stockholm, Sweden will perform the randomization centrally. All inclusion criteria and no exclusion criteria must be met. Inclusion and exclusion criteria are entered into the randomization/registration application, which is a web-based instrument (ALEA). Username and password are required to log in; each investigator authorized to register patients has a personal login user name and password. If all criteria are met, patients are registered, and the allocated patient study number is recorded in the patients' medical file. After randomization, confirmation e-mail will be sent out to the investigator, research nurse and principal investigator. Randomization will be performed by unblinded dedicated nurses not involved in the study in any other aspect. Each participating center

allocates one dedicated nurse (and one back-up nurse) who will be authorized to enter the web-based randomization system. After randomization a unique study number will be generated for each participant. The code list will be retained in a locked area only accessible to the unblinded nurse (-s).

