### 8.3 Data analyses

The primary endpoint, time to start of adjuvant chemotherapy will be analyzed using a linear regression model including the variable treatment. Results will be presented as the mean difference in days together with 95% confidence intervals and a Wald-test p-value. The significance level in the main analysis is set to 5%. Regression models including different clinical factors will also be estimated to take potential confounding into account. All analyses of primary and secondary outcome will be performed according to the intention-to-treat principle but may also be presented as per-protocol. For safety data, patients will be analyzed according to per-protocol approach.

Differences in complications, morbidity and in cardiac and renal impairment will be tested using Chi-square tests of independence. For dichotomous outcomes result will also be presented as differences in proportions together with 95% confidence intervals. Overall survival time will be calculated from the date of randomization to the date of death. For patients still alive, survival time will be calculated from the date of randomization to the date of last visit. Results from the survival analysis will be graphically presented as Kaplan-Meier curves. Proportional hazards regression models will be used to estimate the effect of the intervention on time to death. Results will be presented as hazard ratios 95% confidence intervals and Wald test p-values.

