### 8.4 Power and sample size

If the mean time to start of chemotherapy with standard treatment is 31 days (SD=12) the study needs to recruit totally 182 patients in order to detect a reduction in time to chemotherapy with 5 days (from 31 to 26 days) in the experimental group, using a two-sided significance level of 5% and a power of 80%. To compensate for a possible 20% drop out rate the target sample size is set to 220 patients.

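### Randomisation is stratified by centre but the stated primary model holds treatment only, so precision is left unused if centres differ in days to chemotherapy

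*Protocol*

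**What the plan says.** Design. Protocol section 4.4 says women will "receive either Ropivacaine or saline by equal allocation, 1:1" and continues: "The randomisation procedure will be pre-stratified for participating centre (permuted block design". Centre is the only stratification factor named.

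Primary analysis. Section 8.3 says the primary endpoint "will be analyzed using a linear regression model including the variable treatment". On reporting it adds: "Results will be presented as the mean difference in days together with 95% confidence intervals and a Wald-test p-value".

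Other models. The same section adds: "Regression models including different clinical factors will also be estimated to take potential confounding into account". These models are additional to the primary one, their factors are not named, and the reason given is confounding rather than the stratified design. Overall survival is to be analysed by proportional hazards regression, with no covariates listed.

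Sample size. Section 8.4 assumes a control mean of 31 days, an SD of 12 and a 5-day reduction, and arrives at 182 patients for 80% power at a two-sided 5% level. The SD is a single overall figure, not split into within-centre and between-centre parts.

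**The concern.** Permuted blocks within centre give the two arms nearly the same mix of centres, so a centre that is slow or fast to start chemotherapy largely cancels out of the difference between arms. A model with treatment as its only term does not know this. It counts the spread between centre means as residual noise and computes the standard error as if allocation had ignored centre.

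Where centres do differ, the confidence interval is wider than the design warrants, the test rejects less often than 5% under the null, and precision bought by the stratification is not collected. The endpoint is the date of a scheduled treatment. Sections 5.3 and 6 leave epidural management, surgery and discharge to hospital or clinical routine, so centre differences are plausible. The protocol does not document them.

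**Working it through.** **Inputs.** From section 8.4: difference δ = 5 days, SD σ = 12, two-sided α = 5%, N = 182 evaluable. From section 4.4: 1:1 allocation in permuted blocks within centre. Not in the protocol: the share ρ of total variance lying between centres, the number of centres and the block size. ρ is therefore an assumption, shown over a range, with σ = 12 read as the total SD.

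**Step 1: the plan's own figure.** Per arm, n = 2(1.960 + 0.842)² × 12² / 5² = 90.4, rounded up to 91, so 182 in total. The stated number reproduces. The standard error is 12 × √(4/182) = 1.779 days and 5/1.779 = 2.81, so power = Φ(2.81 − 1.96) = 80.3%.

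**Step 2: effect of leaving centre out.** With near-perfect balance within centres:

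- standard error reported by the treatment-only model: 12√(4/N)
- true standard error of that estimate, which a model with centre would also report: 12√((1 − ρ)4/N)
- overstatement: 1/√(1 − ρ) − 1
- actual type I error, treatment only: 2[1 − Φ(1.96/√(1 − ρ))]
- power, treatment only: Φ((2.81 − 1.96)/√(1 − ρ))
- power, treatment plus centre: Φ(2.81/√(1 − ρ) − 1.96)

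At N = 182:

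| ρ (assumed) | SE, treatment only | SE, with centre | Overstated by | 95% CI half-width, days | Type I error, treatment only | Power, treatment only | Power, with centre |
|---|---|---|---|---|---|---|---|
| 0 | 1.78 | 1.78 | 0 | 3.49 in both | 5.0% | 80.3% | 80.3% |
| 0.02 | 1.78 | 1.76 | 1.0% | 3.49 vs 3.45 | 4.8% | 80.5% | 81.0% |
| 0.05 | 1.78 | 1.73 | 2.6% | 3.49 vs 3.40 | 4.4% | 80.9% | 82.2% |
| 0.10 | 1.78 | 1.69 | 5.4% | 3.49 vs 3.31 | 3.9% | 81.5% | 84.2% |
| 0.20 | 1.78 | 1.59 | 11.8% | 3.49 vs 3.12 | 2.8% | 82.9% | 88.2% |

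Treatment-only power rises slightly with ρ because the total SD is held at 12: the estimate becomes less variable while the reported standard error stays put.

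**Step 3: simulation check.** N = 182, blocks of 4, and 4 or 8 centres (both assumed), 5,000 runs per setting. Simulation error on a 5% rate is about 0.3 points.

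- ρ = 0.10: type I error 3.8% (4 centres) and 4.2% (8 centres) treatment only, against 4.5% and 5.1% with centre. Power goes from 81.6% to 83.8% and from 80.5% to 83.0%.
- ρ = 0.20: type I error 3.5% in both cases treatment only, against 4.8% and 5.1% with centre. Power goes from 83.8% to 88.2% and from 82.5% to 87.1%.
- ρ = 0: the two models agree. Power is 80.2% and 80.3% with 4 centres and 79.3% in both models with 8, so the 3 to 7 extra degrees of freedom cost almost nothing.

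With about 17% random loss after randomisation, which disturbs balance within centres, the treatment-only type I error was 4.1% and 4.3% at ρ = 0.10 and 3.6% and 4.1% at ρ = 0.20. The formula values in the table are therefore upper limits on the distortion.

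**The case against.** A comparison of means in a 1:1 randomised trial is a legitimate primary analysis without covariates. Omitting centre neither biases the estimate nor inflates the type I error; any miscalibration is on the conservative side. That stands, and it makes this a point of efficiency and calibration, not of validity.

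A reader might infer that the trial loses power it was counting on. The figures do not support that: with 182 evaluable women the treatment-only model meets the planned 80% at every assumed ρ. What is forgone is an additional gain of about 0.5 to 3 points for ρ between 0.02 and 0.10. A 20% loss from 220 would leave 176 women and 78.9% power, but that shortfall comes from the drop-out allowance and not from omitting centre.

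A reader might also take the standard error to be too wide in fact. The protocol gives no between-centre variance. Section 1.1.2 describes a generally accepted national window of 3–4 weeks, and section 6 a standardised anaesthesia protocol at all hospitals, either of which could keep centres alike. The claim has to stay conditional. Likewise, the 2.8% type I error at ρ = 0.20 is the perfect-balance limit and not an expected value.

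The survival model might be read as containing the same error. It does not: section 8.3 lists no covariates for it, and silence on a secondary endpoint is not an exclusion of centre.

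Finally, covariate lists are often left to a statistical analysis plan, and one not seen here may add centre. That answers the point only in part. Section 8.3 does not defer the primary model; it states what the model includes, and the one stratification factor is not there.

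**Conclusion.** The mismatch is in the text: section 4.4 stratifies by centre, section 8.3 states a primary model with treatment only, and the sentence on further models with clinical factors does not close the gap. If centres differ, the standard error is somewhat too wide and the test somewhat conservative. For a between-centre share of 2% to 10% this means an overstatement of at most about 1% to 5.4%, and a 95% interval up to about 0.04 to 0.18 days wider on each side (3.49 − 3.45 and 3.49 − 3.31) against a 5-day target. At 20% the overstatement reaches at most 11.8% and the power forgone is about 5 points (88.2 − 82.9). If centres do not differ, nothing is lost.

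These sizes rest on an assumed variance share, a total SD of 12 in both arms, 182 evaluable women and good balance within centres. The direction does not depend on the exact share. This is a modest flaw that is worth correcting because the correction is almost free.

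**What to change.** In section 8.3, define the primary model as linear regression on treatment plus centre, with centre as a fixed effect. State how very small centres are pooled, and fix that rule before unblinding. Report the treatment coefficient, its 95% interval and its Wald p-value from this model. If the unadjusted difference is still wanted, label it supportive. Carry the same definition into the statistical analysis plan.

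The cost is a wording amendment and one degree of freedom per centre beyond the first. The sample size need not change, since 182 is sufficient without the adjustment. Including centre in the survival model as well would be consistent with the design, but it is optional and not part of the error.

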#### **4.5 Blinding and code-breaking**

After allocation has been established, the unblinded nurse then prepares, verifies and label the study drugs in a confined room where both Ropivacaine and Placebo are stored. The syringes and bags for infusion are marked with the patient's unique study number generated at time of randomization. After the intervention/placebo has been prepared their original containers must be put in plastic bag without transparency, closed and then discarded. Both intervention and placebo are color and odorless transparent fluids why blinding can be maintained. The bag for intermittent infusion during the following 72 hours after end of the surgical procedure is covered/masked and secured from opening also marked with patient's study number.

The code list for which treatment the patient was allocated to will be retained in a locked area/cupboard by the unblinded study nurses, not accessible by participating observers or other personnel in the operating rooms, wards or by the attending surgeon, anesthesiologist or oncologist. In this way, full blinding will be achieved at all stages until the end of the study (last patient recruited and followed-up until initiation of adjuvant chemotherapy).

Code-breaking is permitted only if there is a serious negative reaction of IMP to the patient and when determination of the IMP is essential for further management of the patient. The principal investigator should be contacted for code breaking. The contact information to the PI is included in the medical records for each randomized patient. The coordinating investigator will maintain a log of all code-breakings that occur during the trial. The reason for breaking the code must be specified.

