#### 12.1.3 Definition of Suspected Unexpected Serious Adverse Reactions (SUSAR)

Each SAE that is at least possibly related to an IMP is to be classified by the investigator as expected or unexpected. An SAE that is at least possibly related to an IMP, and **unexpected**, is defined as a Suspected Unexpected Serious Adverse Reaction (SUSAR). It is expected if it is already known from earlier trials or is mentioned in relevant documents (Investigator's Brochure, SPC).

The SUSAR are reported up to 30 days after end of study treatment (33 days postoperatively)

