#### 12.4.3 Reporting of Suspected Unexpected Serious Adverse reactions (SUSAR)

The sponsor is responsible for registering of all relevant information regarding suspected, unexpected, serious adverse reactions in the EudraVigilance database and for notifying the Ethics committee.

The sponsor is responsible for informing all investigators of SUSARs that have occurred. Reporting of any SUSAR will be done on the CIOMS form that is sent to the Medical Products Agency, as sponsor is not able to report this electronically to the EudraVigilance database.

A SUSAR that resulted in death or was life threatening must be registered promptly, or within 7 days after occurrence or sponsor awareness. Relevant subsequent information should be registered within the following 8 days. All other SUSARs should be reported as soon as possible or within 15 days after sponsor awareness.

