### 12.8 Safety reference information

For reference safety information of the investigational medicinal products, reference is given to the SmPCs. Assessment of an AE/SAE as expected or unexpected will be made with reference to the SmPC.

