### 15.6 Quality Control and Monitoring

To assure that the study is conducted in accordance with the study protocol, that study data is collected properly, that documentation and reporting is done in accordance with ICH-GCP (Good Clinical Practice) and additional ethical and regulatory requirements, the study will be monitored by a qualified professional not involved in the study prior to study start, during, and after study termination. The extent of monitoring will be described in a monitoring plan, based on the sponsor SOPs, protocol and regulatory requirements, which will be approved by the Sponsor. Study conductance, source data, drug accountability, adherence to GCP, and regulatory requirements will be monitored. Monitoring will be performed by experienced personnel at CTO, Centre for Clinical Cancer studies, Theme Cancer, Karolinska University Hospital Solna, which in no way contribute to the actual implementation of the study. There will be separate monitors for blinded and unblinded data respectively, to maintain the double-blinding of the study.

The investigator and other responsible study personnel must be available during the monitor visits and should prepare appropriate material as source data verification documents and CRFs for the monitor. Study personnel should devote enough time to these processes. The investigator will ensure that the clinical investigation participants are aware of and consent that personal information may be scrutinized during the data verification process as part of clinical investigation-related monitoring and auditing by properly authorized persons associated with inspection by domestic and/or foreign regulatory authority (-ies). However, participation and personal information should be treated as strictly confidential to the extent that the applicable law permits and not be publicly available.

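### Protocol 4.5 bars opening the code for SUSAR reporting unless the woman's care requires it, so some SUSARs must go to the agency and ethics committee with treatment unknown

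*Protocol*

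**What the plan says.** Protocol 4.5 sets the rule for breaking the code: "Code-breaking is permitted only if there is a serious negative reaction of IMP to the patient and when determination of the IMP is essential". The rest of that sentence ties the second condition to how the woman is managed afterwards. The request goes to the principal investigator, and the coordinating investigator logs each opening with its reason. The same section says that "full blinding will be achieved at all stages until the end of the study", which it defines as the point when the last recruited woman has been followed to the start of chemotherapy. The allocation list is "retained in a locked area/cupboard by the unblinded study nurses, not accessible by participating observers" or by the treating clinicians.

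Section 12.1.3 gives classification to the investigator: "Each SAE that is at least possibly related to an IMP is to be classified by the investigator as expected or unexpected". Section 12.8 names the reference: "Assessment of an AE/SAE as expected or unexpected will be made with reference to the SmPC". On timing, 12.1.3 says: "The SUSAR are reported up to 30 days after end of study treatment (33 days postoperatively").

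Under 12.4.3 the sponsor reports SUSARs to the agency on a CIOMS form and notifies the ethics committee, within 7 days for fatal or life-threatening cases and 15 days for others. It adds: "The sponsor is responsible for informing all investigators of SUSARs that have occurred". It does not say whether the allocation is obtained first.

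Section 15.6 provides unblinded oversight of a kind: "There will be separate monitors for blinded and unblinded data respectively, to maintain the double-blinding of the study". It gives the unblinded monitor no task in SUSAR reporting. Section 14.1 names the coordinating investigator as sponsor.

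**The concern.** The code-breaking rule serves one purpose, the care of the individual woman. SUSAR reporting serves another: telling the agency and the ethics committee whether the study drug may be causing unexpected serious harm. The second purpose needs the allocation in cases where the first does not, and 4.5 makes no room for that.

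At stake is the attribution of rare serious events while women are still being randomised. If the allocation is missing from the report, an event in a woman who received only saline in the peritoneum can stand on file as a suspected reaction to intraperitoneal ropivacaine, indistinguishable from one in a woman who received the drug. The annual safety report (12.7) and the ground in 4.7 for early termination because of IMP-related serious events both draw partly on such cases. The protocol text describes no unblinded safety board that would sort them out.

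**Working it through.** There is no plan figure to reproduce. The check is whether the sections on blinding and on safety reporting can all be followed at once.

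**Step 1. The rule in 4.5.** It is exclusive and has two conditions, both of which must hold: (a) a serious reaction to the IMP, and (b) knowledge of the allocation is essential for the woman's care.

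**Step 2. Apply it to a SUSAR.** By 12.1.3 a SUSAR is serious and at least possibly related to the IMP, so (a) is normally met and (b) decides.
- If (b) holds, the code may be opened and the report can carry the allocation.
- If (b) fails, because she has died, the event has resolved, or its treatment is the same in both arms, 4.5 forbids opening the code. The report under 12.4.3 must then go out without the allocation.

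**Step 3. Look for another route.** Sections 12.1.3, 12.4.3, 12.7 (annual report), 12.8 and 15.6 contain no unblinding step tied to reporting. Section 4.4 restricts the list to the unblinded nurses. No second ground for opening the code appears.

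**Step 4. How far can blinded judgement separate the arms?** The entry threshold is low: 12.2.2 rates causality as possible whenever a link is conceivable and cannot be ruled out. Both arms also receive ropivacaine epidurally.
- Epidural (5.3): usually 4 to 14 ml/h at 2 mg/ml, which is 4 × 2 = 8 to 14 × 2 = 28 mg/h. Over 24 h this is 8 × 24 = 192 to 28 × 24 = 672 mg/day.
- Postoperative study drug (IMP page and 5.1): 10 ml × 2 mg/ml = 20 mg every other hour. Over 72 h that is 36 × 20 = 720 mg, or 720/3 = 240 mg/day.
- Ratio of epidural to postoperative intraperitoneal daily amount: 192/240 = 0.8 to 672/240 = 2.8.

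A woman given saline may thus receive a comparable or larger daily amount of the same drug by the epidural route. A blinded investigator will often be unable to dismiss a link, so events in saline recipients can pass the threshold.

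**Step 5. What would the allocation settle?** For a saline recipient it rules out the intraperitoneal study drug. It does not rule out epidural ropivacaine. The gain is correct attribution to the investigational use of the drug, not a final answer on causality.

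**Step 6. Which counts depend on this?** Section 4.7 refers to serious events related to the IMP, and the annual report summarises all SAEs and SUSARs. Both include serious events that are related but expected, which are not SUSARs. Opening the code for SUSARs alone would correct only part of either count.

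**The case against.** The strongest case on the other side has four parts.

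*Section 12.4.3 is silent.* It does not say that reports go out blinded, and 4.5 may be read as governing only requests from treating staff, not people who already hold the list. The silence is real. But 4.5 is worded as an exclusive permission and makes no exception for reporting. A separate safety procedure that opened the code for reporting would contradict it. Hence the finding is a conflict to be reconciled, not a detail left to another document.

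*Blinded causality assessment is ordinary, and 12.1.3 asks only for a possible relation.* This stands. Blinded classification is not criticised here, nor are blinded notices to investigators, which protect the trial. The gap lies in what the agency and the ethics committee are told afterwards.

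*The epidural exposure cuts both ways.* This also stands. It weakens blinded judgement, but it means that a saline allocation does not clear ropivacaine as a cause. The remedy has to say so.

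*Adding the allocation could unblind the coordinating investigator, who as sponsor files the form, and 4.4 keeps the randomising nurses out of every other study task.* Correct. The change therefore needs a defined route.

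A reader might infer that every SUSAR is reported blinded. The text does not support that: where care depends on the allocation, the code may be opened. A reader might also note that 33 − 3 = 30 of the 33 reporting days (91%) follow the 72 h of dosing, and conclude that most SUSARs fall outside the rule. That is a share of calendar days, not of events, and nothing in the protocol says that reactions are spread evenly over time. Likewise, the expectation that half of the blinded SUSARs come from saline women when there is no true excess only restates the 1:1 allocation.

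**Conclusion.** The concern holds in a limited form. Sections 4.5 and 12.4.3 together oblige the sponsor to report without the allocation any SUSAR whose management does not turn on it. Such a report can present an event in a saline recipient as a suspected reaction to the intraperitoneal study drug.

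The size cannot be given in numbers. The protocol states no expected number of SUSARs; reactions listed in the SmPC count as expected, and 9.1 reports no systemic toxicity in the 40-patient pilot, so there may be few. Few cases make each attribution matter more, but the documents do not support saying that one or two would decide the safety judgement.

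The conclusion rests on two assumptions: that the restriction in 4.5 means what it says for everyone in the trial, and that no other binding text overrides it. It does not rest on any outside reporting rule. The stopping ground in 4.7 and the annual report are affected only in part. The primary endpoint and its analysis are not touched. The change should be made because it improves safety attribution at little cost.

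**What to change.** Reconcile 4.5 and 12.4.3 by adding a second ground for opening the code, limited to regulatory reporting, and leave the existing patient-care ground as it is:

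- For each SAE classified as a SUSAR on blinded assessment, a person already unblinded obtains that woman's allocation before the report is filed. The unblinded nurse holds the list and would pass the entry to the unblinded monitor or the trials unit. Section 4.4 should be adjusted to allow this one task.
- The allocation goes only to the agency and the ethics committee, by a route that the coordinating investigator does not see. This must be written down, because that person is the sponsor and would otherwise file or read the form.
- Notices to investigators under 12.4.3 stay blinded.
- The opening is entered in the existing code-break log with its reason but without the treatment.
- For a saline recipient, the report says that the event is not a reaction to intraperitoneal ropivacaine and describes epidural ropivacaine as a possible cause where relevant.

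The cost is short additions to 4.4, 4.5 and 12.4.3, a small separate reporting route, and a few allocations handled by staff who are already unblinded. Surgeon, anaesthesiologist, oncologist and coordinating investigator remain blinded. Related but expected SAEs stay blinded too, so the counts behind 4.7 and the annual report improve only partly, and the text should not claim more.
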